# Nasal high-flow compared to non-invasive ventilation in treatment of acute acidotic hypercapnic exacerbation of chronic obstructive pulmonary disease—protocol for a randomized controlled noninferiority trial (ELVIS)

**DOI:** 10.1186/s13063-021-05978-z

**Published:** 2022-01-10

**Keywords:** Chronic obstructive pulmonary disease, COPD, Nasal high-flow, Non-invasive ventilation, Acidotic hypercapnic exacerbation, intubation, Randomized controlled trial, RCT

## Abstract

**Background:**

Acute exacerbations of chronic obstructive pulmonary disease (AECOPD) have a major negative impact on health status, rates of hospitalization, readmission, disease progression and mortality. Non-invasive ventilation (NIV) is the standard therapy for hypercapnic acidotic respiratory failure in AECOPD. Despite its beneficial effects, NIV is often poorly tolerated (11–34 % failure rate). An increasing number of studies have documented a beneficial effect of nasal high-flow (NHF) in acute hypercapnia. We designed a prospective, randomized, multi-centre, open label, non-inferiority trial to compare treatment failure in nasal NHF vs NIV in patients with acidotic hypercapnic AECOPD.

**Methods:**

The study will be conducted in about 35 sites in Germany. Patients with hypercapnic AECOPD with respiratory acidosis (pH < 7.35) will be randomized 1:1 to NIV or NHF. The primary outcome is the combined endpoint of intubation, treatment failure or death at 72 h. The switch from one to the other device marks a device failure but acts as a rescue treatment in absence of intubation criteria. A sample size of 720 was calculated to have 80% power for showing that NHF is non-inferior to NIV with a margin of 8 percentage points. Linear regression will be used for the confirmatory analysis.

**Discussion:**

If NHF is shown to be non-inferior to NIV in acidotic hypercapnic AECOPD, it could become an important alternative treatment.

**Trial registration:**

ClinicalTrials.gov, NCT04881409, Registered on May 11, 2021

**Supplementary Information:**

The online version contains supplementary material available at 10.1186/s13063-021-05978-z.

## Background

Chronic obstructive pulmonary disease (COPD) is a common, preventable and treatable disease characterized by persistent respiratory symptoms and airflow limitation due to airway and/or alveolar abnormalities usually caused by significant exposure to noxious particles or gases. COPD is a leading cause of morbidity and mortality worldwide. Prevalence of COPD is much higher in smokers and ex-smokers, in subjects of ≥ 40 years of age, and in men. Approximately, three million deaths occur annually worldwide. The prevalence of COPD is expected to rise in the decades ahead because of continued exposure to COPD risk factors and ageing of the population [1–3].

The Global Burden of Disease Study reports a prevalence of 251 million cases of COPD in 2016 [1, 4]. 3.17 million deaths were reported to be caused by COPD in 2015 (5% of all deaths). Most patients with COPD develop typical exacerbations of the disease during their lifetime. In severe AECOPD hospitalization is required. Data from the European COPD audit in 13 countries and 422 hospitals [4] monitored 16,016 patients. Of those patients who had blood gas checks at the time of hospital admission (*n* = 13,069), 5933 had hypercapnia (45.4%) and 2452 (18.8%) had respiratory acidosis.

Acute exacerbations of chronic obstructive pulmonary disease (AECOPD) episodes have a major negative impact on health status, rates of hospitalization, readmission, disease progression and mortality [5]. AECOPD is characterized by increased dyspnoea, increased sputum purulence and volume. Severe AECOPD can lead to acute hypercapnic acidotic respiratory failure, a life-threatening condition. The mortality of AECOPD is severe with 183 deaths of 1000 patients with hypercapnic AECOPD and 341 of 1000 will be intubated and mechanically ventilated [5].

Non-invasive ventilation (NIV) is the standard therapy for hypercapnic acidotic respiratory failure in AECOPD [6]. Solid evidence of its effectiveness has been generated for more than two decades with RCTs demonstrating rapid improvement in blood gases, respiratory rate, need for intubation, length of hospital stay and mortality [5–8]. Despite its beneficial effects, NIV is often poorly tolerated (11–34 % failure rate) [5, 9, 10]. In most cases, the adaptation is difficult and time-consuming and may require patient sedation.

Nasal high-flow (NHF) provides warmed and humidified gas administered through larger bore soft nasal prongs. The almost saturated and warmed gas flow is the basis of good tolerance even at high flow rates (30–60 l/min). NHF results in only a small increase in airway pressure (further reduced by opening the mouth). NHF reduces minute volume, lowers respiratory rate and decreases the work of breathing. Exhaled gas in the upper airways is rapidly washed out and thus physiological dead-space is reduced [11–15]. The high flow rates delivered by NHF are sufficient to cover even high peak inspiratory flows, thereby avoiding the admixture of ambient air.

In a recent study, NHF was found to be superior to standard nasal prongs (SNP) and NIV in patients with severe hypoxemic respiratory failure with regard to intubation rates and mortality [16]. The reintubation rate in the NHF arm was non-inferior or better compared to either venturi mask, SNP or NIV respectively [17, 18] in a mixed hypoxemic population. Most data relating to effectiveness of NHF consider post-extubation respiratory failure also including respiratory acidosis defined as pH < 7.35 and PaCO_2_ > 45 mmHg. Interestingly, in the two studies by Hernandez et al., a trend of decreasing respiratory acidosis was reported during NHF therapy [18]. These trends were found in comparison to conventional oxygen and non-invasive ventilation (NIV).

A number of studies and case reports with hypercapnic patients are being reported [11, 12, 14, 19]. Most of these studies investigating the effects of NHF on chronic hypercapnia have been conducted in COPD patients. The first study was the investigation by Bräunlich et al. in 2013 [12]. This mechanistic study was the first to describe the changes in respiratory patterns in healthy volunteers, patients with COPD and lung fibrosis. Patients with stable values of capillary pCO_2_ using NHF for 8 h during the daytime with a flow of 24 l/min showed a decrease in capillary pCO_2_ by 0.69 ± 0.2 kPa [12]. The reduction in hypercapnia was seen despite a decrease in respiratory rate and minute volume. Significant changes were also found in patients with interstitial lung disease (ILD). Another study by our group confirmed these results and documented a decrease in capillary pCO_2_ in 54 COPD patients [20]. A major finding was a greater extent of decarboxylation by using higher flow rates. The mean value decreased from 91 ± 6.7% at 20 l/min to 87.4 ± 6.2% at 30 l/min after a 2-h treatment period. In agreement with the study by Frizzola et al., we observed a decrease in hypercapnia that was a flow-dependent [21]. A study by Pisani et al. investigated patients with COPD and reported a decrease in arterial pCO_2_ at a flow rate of 20 and 30 l/min with the mouth closed. With 30 l/min but not with 20 l/min, a concomitant decrease in pO_2_ was observed with an accompanying decrease in respiratory rate [22]. The retrospective clinical study by Jeong et al. revealed the potential decrease in hypercapnia during NHF therapy in a cohort of 46 patients with and without COPD in an emergency department [23]. Most of the patients in the hypercapnic group had a AECOPD. Hypercapnia decreased significantly with an increase in paO_2_. But this observation was only found in hypercapnic patients.

Our TIBICO trial is a 6 week, cross over study using either NHF or NIV in stable hypercapnic COPD patients without recent exacerbation. The main result was that NHF was similar to NIV in terms of decreasing hypercapnia and quality of life. This was the first randomized controlled trial indicating the stable effect of respiratory support in hypercapnic patients by NHF [14]. Taking this study into account together with CO_2_ wash-out studies, we concluded that AECOPD patients might benefit from NHF as much as from NIV.

Few studies regarding the use of NHF have been published in acute AECOPD. A couple of recent trials appear to confirm our hypothesis in mixed populations with a subset of hypercapnic AECOPD patients with significant improvements in blood gases during NHF therapy [24, 25]. In a pilot study retrospectively looking at acidotic AECOPD patients that did not tolerate prior NIV and prospective RCTs, we and others observed improvements with NHF that were comparable to those generally observed with NIV [19, 26]. The study by Cortegiani et al. investigated patients with acidotic hypercapnic AECOPD. The primary endpoint was the decline in hypercapnia compared to NIV. They found no difference after 2 h between the two devices after randomization of 80 patients [27].

The main objective of the ELVIS clinical trial will be a direct comparison of nasal high flow and non-invasive ventilation (via oral/nasal mask) in hypercapnic, acidotic AECOPD patients.

## Methods

### Study design

ELVIS is an investigator initiated trial funded by the German Ministry for Education and Research (BMBF KS2018-073). In a legal sense, this trial is regulated by the European Medical Devices Law for use of approved devices in their indication. The legal basis for the study is the German Medical Devices Act (MPG §23b), valid before the MPDG came into force. As such, there is cannot be a legal sponsor. However, Leipzig University is the “Responsible Institution,” and neither the university qua university nor the BMBF played any part in study design. Furthermore, they will play no part in data collection, management, analysis and interpretation of data; writing of the report; and the decision to submit the report for publication. The trial is designed as a prospective, randomized, multi-centre, open label, non-inferiority trial. Blinding is not possible because of the different nature of the two different devices, but the endpoints were chosen to be as objective as possible to avoid potential bias. The analysts will not be blinded. The study will be conducted in about 35 university and community hospitals in Germany involving the pneumology and emergency wards as well as ICU; see supplement for the list of intended sites.

Each trial site receives a study-specific NHF device (through public funds), although other specified devices may also be used. The handling of the devices is carried out according to the manufacturer's instructions. The protocol was approved by the Ethics Committee of all participating centres. The study was registered at ClinicalTrials.gov in May 2021 (NCT04881409). Study monitoring, data handling and organization of the study will be provided by Clinical Trials Centre from the University of Leipzig, Germany.

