In case of premature termination of therapy, it is necessary to document the date (as exactly as possible), the reason of termination and the current condition of the patient. Therefore, the eCRF “End of study (ES)” has to be completed for each patient. Data entry to this eCRF page will trigger an automatic report to the responsible trial team members at the ZKS Leipzig.

After a patient has been enrolled, it is the investigator's responsibility to avoid protocol violations in order to obtain unbiased data for the trial. Those protocol violations deemed to be major are defined by the risk analysis performed before and during trial implementation and will be further detailed in separate documents belonging to the risk assessment/monitoring plan. This list can be augmented in the course of the trial. Major protocol violations will be reported to the coordination centre Leipzig, which will inform the co-ordinating investigator. All protocol violations will be documented and discussed with the responsible biometrician before closing the data base and carrying out the statistical analysis. The investigator must ensure that the recorded data are documented as per protocol. Minor variations are inevitable in clinical routine but must be documented together with a justification.

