The full analysis set (FAS, based on the intention-to-treat (ITT) strategy) is defined to comprise all randomized patients with AECOPD and started on ventilatory support. If, for example, pneumonia is detected within 48 h (nosocomial), such patients will not be included in the final analysis, since the initial AECOPD diagnosis is found to be erroneous. Patients who test positive for SARS-CoV-2 within 48 h will not be included in the full analysis set. For the confirmatory analysis, linear regression with the stratification variables and the arm as covariates will be used and where the dependent variable will be coded as 0, 1. A 95% two-sided Wald confidence interval for the arm term can then be interpreted in terms of absolute risk and the null hypothesis is rejected if it does not cross the non-inferiority margin. As a sensitivity analysis, a two-sided 95%-Wilson confidence interval for the difference in proportions will be calculated. Only few missing data regarding all relevant endpoints are expected given the rather short period of observation. Nevertheless, conservative imputations will be performed independent of treatment arm. Further sensitivity analyses are planned to adjust for covariates, possibly imbalanced baseline characteristics between groups and/or protocol deviations in multivariable regression models, e.g. for (components of) the primary endpoint and/or in subgroups, which arose from stratification criteria. Furthermore, the odds ratios from logistic regression will be computed to have a relative risk measure in addition to the absolute one, as recommended by statistical guidelines.

Absolute risk differences of major secondary endpoints will be analysed in the same way as the primary endpoint. Kaplan-Meier curves/results of logrank tests will be presented for 28 and 90 days mortality. We expect the time to death to be (nearly) always available. Ventilator-free hours (until 72 h assessment) and SRI and SGRQ at 28 days will be analysed by a linear regression model including randomization arm as factor and stratification criteria as covariates. SRI and SGRQ cannot be determined at baseline due to the patients’ state.

Neither imputation of missing values nor adjustments for multiple testing are planned for secondary/safety endpoints. No interim analysis is planned.

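### An open-ended exclusion after randomisation for a mistaken AECOPD diagnosis, with analysts declared unblinded and no masked decision stated, can be judged with arm and outcome known

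*Protocol article*

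**What the plan says.** All places are in the Methods of the protocol article.

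- **Study design.** The trial is open label, for this reason: "Blinding is not possible because of the different nature of the two different devices". The section then adds: "The analysts will not be blinded".
- **Sample size and statistical analysis.** The full analysis set is described as following the intention-to-treat strategy, yet it "is defined to comprise all randomized patients with AECOPD and started on ventilatory support". The diagnostic condition is applied after randomisation: "If, for example, pneumonia is detected within 48 h (nosocomial), such patients will not be included in the final analysis". A second exclusion, a positive SARS-CoV-2 test within 48 h, rests on a test result. The confirmatory model is fixed (arm and stratification variables), and imputation is to be conservative and the same whatever the arm.
- **Study endpoints.** The primary endpoint is device switch, intubation or death within 72 h.
- **Randomization, recruitment and data collection.** On deviations: "All protocol violations will be documented and discussed with the responsible biometrician before closing the data base and carrying out the statistical analysis". On the catalogue of major violations: "This list can be augmented in the course of the trial".
- **Interventions.** Statistical monitoring of the database runs at regular intervals and checks the documented reasons for switching device.

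**The concern.** The reason given for the open-label design applies to patients and bedside staff. It does not explain why those who review listings and settle the analysis set must know the allocation. The statement about analysts is therefore a choice, and the article describes no exception for the one decision where it matters most: whether a randomised patient counts.

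That decision is left loose in three ways. The ground is open-ended, since pneumonia only illustrates it. No decision-maker is named, masked or otherwise. And the evidence may arrive up to 48 h after entry, when the patient may already have switched device, been intubated or died.

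If exclusions then fall unevenly on failures in one arm, the estimated difference moves. In a non-inferiority trial, losing NHF failures moves it towards the favourable conclusion. Even if every decision is sound, an open-label trial without a masked decision cannot readily show this afterwards.

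**Working it through.** **1. The plan's own sample size, to fix the number per arm.** Inputs from Sample size and statistical analysis: 15% failure in both arms, margin 0.08, 80% power, upper end of a two-sided 95% interval, continuity correction.

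- Without correction: n = 2 × 0.15 × 0.85 × (1.960 + 0.842)² / 0.08² = 312.7, so 313 per arm.
- With correction: (313/4) × [1 + √(1 + 4/(313 × 0.08))]² = 337.5, so 338 per arm or 676 in total.

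This agrees with the stated 680 to within rounding. Power at 340 per arm is 80.3% with the correction. So 340 per arm is used below, with 51 NIV failures (0.15 × 340).

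**2. Timing.** The exclusion window (48 h) ends 24 h before the endpoint window (72 h). The two overlap throughout the first 48 h, so the endpoint can precede the finding that triggers exclusion.

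**3. How few patients matter.** The upper limit is d + 1.96 × √[p₁(1 − p₁)/n₁ + p₀(1 − p₀)/n₀], with d = p₁ − p₀, NHF as 1 and NIV as 0. The planned model also adjusts for the stratification variables; the unadjusted form is used for illustration. All failure counts and numbers removed are assumptions.

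| NHF | NIV | d (points) | SE (points) | Upper limit (points) | 8-point margin |
|---|---|---|---|---|---|
| 60/340 | 51/340 | 2.65 | 2.83 | 8.20 | missed |
| 59/339 (1 NHF failure removed) | 51/340 | 2.40 | 2.83 | 7.94 | met |
| 59/339 | 50/339 (1 failure removed in each arm) | 2.65 | 2.82 | 8.18 | missed |
| 62/340 | 51/340 | 3.24 | 2.85 | 8.83 | missed |
| 58/336 (4 NHF failures removed) | 51/340 | 2.26 | 2.83 | 7.81 | met |

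The third row shows that the harm comes from imbalance: removing one failure from each arm leaves the conclusion unchanged.

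**4. Effect on error.** Take true rates at the margin (23% NHF, 15% NIV, 340 per arm). Sum the binomial probabilities of every outcome in which the upper limit falls below 8 points after k NHF failures have been removed:

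| k removed, all NHF failures | One-sided type I error |
|---|---|
| 0 | 2.55% |
| 3 | 4.46% |
| 5 | 6.25% |
| 10 | 13.23% |

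This is a worst case, because every removal is a failure and all are in one arm. The article gives no expected number of diagnostic exclusions. Its nearest figure is the drop-out allowance, 720 − 680 = 40 patients, and it does not say whether that covers them.

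**The case against.** **The strongest reply** is that the article only discloses that analysts are unblinded, in a trial that is openly unblinded, and that a masked review of the data may be set out in the full protocol or SAP, which are not shown. A bare absence of detail would indeed be no finding. But the article states that analysts will not be blinded and makes no exception, and it words the exclusion open-endedly. A masked decision in another document would have to qualify that statement.

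**A reader might infer more than the text supports:**

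- *That the biometrician decides who is in the analysis set.* No section says so. Violations are discussed with the biometrician, and the exclusion has no named decision-maker.
- *That the violation list opens the same door.* The list can grow during the trial, but nothing removes a patient from the full analysis set for a violation. Deviations enter only through sensitivity analyses.
- *That confirmatory covariates or imputation can be chosen with the results in view.* The covariates are fixed, and imputation is stated to be conservative and independent of arm. Adjustment for imbalance belongs to sensitivity analyses only.
- *That all judgements wait until the data are complete.* The deviation discussion is placed before database closure. This limits knowledge of outcomes but does not remove it, because monitoring of the accumulating data already looks at reasons for switching.

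**Two practical objections stand and narrow the remedy.** Pneumonia is diagnosed by site staff who know the device, so masking a central decision does not mask the diagnosis. And compliance with the switching criteria cannot be judged with the switch hidden, so masking suits analysis-set membership but not every violation.

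The removals in the working are also suppositions. They show how sensitive the test is, not what will happen.

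**Conclusion.** The point holds in a narrow form. The article declares its analysts unblinded and allows randomised patients to be dropped on an open-ended diagnostic ground, within a window that overlaps the endpoint, with no masked decision stated. Under the assumptions in the working, one unbalanced exclusion can carry a borderline result across the margin (8.20 to 7.94 points), and four can do so from 8.83 (to 7.81). Results far from the margin would not be affected by so few.

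This is a cheap safeguard worth adding, not a flaw that invalidates the design. It does not show bias or intent, and it does not extend to the confirmatory model, the imputation rule or the handling of major violations.

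**What to change.** 1. **Close the list.** In Sample size and statistical analysis, replace the example with a complete list of grounds for exclusion from the full analysis set, each resting on information from before randomisation or on an objective test finding. This matters because the diagnosing staff cannot be masked.
2. **Mask the decision.** In Study design, qualify the statement on analysts: membership of the full analysis set is decided and signed before database lock, on listings without arm, device parameters or primary outcome, by persons not involved in unmasked monitoring of those patients. Allocation is merged afterwards. Limit this to set membership, so that switch-related violations can still be reviewed with the switch visible.
3. **Show the effect.** Report the primary analysis in all randomised patients as a sensitivity analysis.

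Cost: one masked extract, with fields that reveal the device (including free text) dropped, and reviewers who have not seen those patients' monitoring data. If the monitoring and review staff overlap, someone else must be assigned. The sample size, the endpoint and the confirmatory model do not change.

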### Study population

Patients are eligible for the study if they suffer from AECOPD in the absence of other causes of respiratory failure. Investigators from the pulmonology or emergency wards or from the intensive care unit will briefly describe the trial and obtain informed consent. A concise consent for is available if treatment has to begin imminently, and the full consent is then required at a later point in time. On the consent form, participants are informed in detail about data handling and storage. This trial does not involve collecting biological specimens for storage.

Specific eligibility criteria are as follows.

*Inclusion criteria*
Acute hypercapnic exacerbation of chronic obstructive pulmonary disease with respiratory acidosis (pH < 7.35)pCO_2_ > 45 mmHgage ≥ 18 yearsWritten informed consent

*Exclusion criteria*
Immediate need for intubationpH < 7.15BMI ≥ 35 kg/m^2^Established home-NIV or home-CPAPEnd-stage disease with DNI/DNR orderDiseases that could influence the primary endpoint: e.g. acute heart infarction, cardiogenic lung oedema, acute and massive lung embolism (hypertensive), chronic dialysis with metabolic acidosis, unstable rib fracture influencing ventilation, injury to the face prohibiting use of a face maskAcute disease that precludes participation in the trialTracheotomized patientsPsychological/mental or other inabilities to supply required informed consentParticipation in other interventional trialsSuspected lack of compliance

